## Abstract

**Background:**

Psychophysiological stress and decreased well-being are relevant issues during prolonged social isolation periods. Relaxation practices may represent helpful exercises to cope with anxiety and stressful sensations.

**Objective:**

The aim of this research protocol is to test whether remote relaxation practices such as natural sounds, deep respiration, and body scan meditation promote relaxation and improved emotional state and reduce psychomotor activation and the preoccupation related to the coronavirus disease (COVID-19) pandemic.

**Methods:**

The study population will consist of 3 experimental groups that will randomly receive one of 3 internet-based audio clips containing a single session of guided breathing exercise, guided body scan exercise, or natural sounds. The participants will listen to the fully automated audio clip for 7 minutes and complete pre-post self-assessment scales on their perceived relaxation, psychomotor activation, level of worry associated with COVID-19, and emotional state. At the end of the session, the participants will also be asked to provide qualitative reports on their subjective experiences.

**Results:**

Analyses will be performed to test the differences in the efficacy of the different audio clips in an internet-based intervention on 252 participants (84 per group), investigating whether natural sounds or remote guided practices such as deep respiration and body scan meditation positively enhance the participants’ perceived psychological state.

**Conclusions:**

The study will provide information on if and to what extent guided practices can help in reducing psychological side effects related to social isolation during the COVID-19 pandemic.

**International Registered Report Identifier (IRRID):**

PRR1-10.2196/19236

## Introduction

### Background

The world is facing a new health emergency: coronavirus disease (COVID-19), an infectious disease caused by a newly discovered coronavirus [1].

The COVID-19 pandemic is the first pandemic to occur in the 21st century. Therefore, the majority of the world's population is living with an entirely new experience that has never happened in their lifetime. Since mid-March, Italy has faced a strict lockdown. For an extended period of time, people have been forced to live either alone or in “bubbles” with only a few family members or a partner. In such conditions, it is not difficult to assume that people will feel lost and will experience loneliness and social isolation. These conditions may reduce health and mental well-being, thus affecting vital functions (eg, sleep quality), social connectedness, perceived support, and psychological status [2-4]. A recent rapid review on the effects of the quarantine [5] underlines that society is facing several negative cognitive and emotional problems, such as confusion, poor concentration, irritability, insomnia, distress, frustration, and anger. People are worried about the quarantine duration, insufficient information provision, economic problems, and stigma. These negative effects may impact individuals’ bio-psycho-social functioning and lead to depressive or posttraumatic stress symptoms [5,6].

The lack of a vaccine for COVID-19, the high chance of contagion, and the severity of symptoms—which often lead to death—increase risk perception related to the pandemic. In all high-risk situations, cognitive and rational thinking interact with emotional appraisals, thus affecting people’s state of mind; individuals feel vulnerable and may experience fear for themselves and for their loved ones [7,8]. Both physical and psychological dimensions are affected by the sense of uncertainty and the threat of contracting the virus. Under such conditions, it is not uncommon for people to also experience psychophysiological hyperarousal, which causes them to pay excessive attention to their bodily sensations and enhances their perceptions [9]. Overall, COVID-19 and social isolation have led to negative side effects, causing widespread concern and psychophysiological reactions [10].

Starting from these premises, it is necessary to develop an intervention to investigate people’s psychosocial conditions and reduce possible psychophysiological activation; due to the current circumstances, such an intervention must be internet-based.

Previous studies demonstrated that interventions based on natural sounds, respiration, and meditation may help individuals to alleviate the effects of stress by reducing physiological arousal and restoring autonomic balance [11-14]. In fact, listening to natural sounds significantly reduces human stress processes [13,15]. On the other hand, guided relaxation techniques are widely used to produce a deep state of relaxation and enhance physical and emotional well-being. Deep breathing exercises and focusing attention on body perception are two of the main techniques used to reduce hyperarousal and achieve a more relaxed condition. Deep breathing can be also defined as “an efficient integrative body-mind training for dealing with stress, anxiety and psychosomatic conditions” [16]; it may help people to slow their breathing, take in more oxygen, and reduce the use of their shoulder, neck, and upper chest muscles, thus achieving better emotional balance and social adaptation [17]. On the other hand, body scan meditation aims to focus attention on different parts of the body and help people become aware of their bodily sensations, such as pain, tension, warmth, or relaxation [18,19]. We chose to employ these two techniques because they involve different cognitive and psychophysiological processes. In the present study protocol, we aim to test and compare the efficacy of natural sounds, breathing regulation, and body scan meditation to assess which intervention is the most effective for the target population. Applying these interventions to people forced into mandatory social isolation may help them become more aware of their mind-body condition and reduce negative effects. Moreover, scientific studies have shown that online relaxation techniques as well as in-person programs achieve significant results; these findings may support the implementation of remote interventions, which are currently a necessary feature of proposed programs [20,21]. However, a comparison of natural sounds, respiration, and body scan meditation techniques in internet-based interventions is still lacking in the literature.

### Objective

The aim of this study is to test the difference in the efficacy of three audio clips related to three relaxation practices (deep breathing, body scan meditation, and natural sounds). We expect to find a decrease in the participants’ levels of psychomotor activation/stress and of preoccupation with thoughts related to COVID-19 as well as enhanced relaxation levels and emotional state after exposure to all the audio clips; we also expect that the guided techniques (deep breathing and body scan) will have greater effects on the abovementioned dimensions than natural sounds.

## Methods

### Participants and Procedure

The invitation to take part in the study will be published on social media webpages (WhatsApp, Facebook, LinkedIn, and Instagram). The readers will be informed about the general aim of the study and that the study is conducted by researchers from the University of Milan. Potential participants will be encouraged both to take part in the study and to share the invitation with their acquaintances. The invitation will contain a link to the Qualtrics platform, where a more detailed description will be available.

The eligibility criteria to take part in the study will include being more than 18 years of age, being a proficient Italian speaker, not suffering from any impairment affecting auditive abilities, and having an appropriate level of computer literacy. Before taking part in the study, participants will be asked to read and complete an online consent form. The document will be shown and will be downloadable in .pdf format, and the participant will be asked to give their consent online. The document has already been redacted according to national legislation and by following the guidelines of the Ethical Committee of the first author’s university.

The participation in the study will consist of 3 main parts: 1) completing a short questionnaire requesting background information and a preintervention evaluation, 2) listening to a 7-minute audio clip, and 3) completing the post-intervention evaluation. The estimated time for participating in the study (completing the three parts) will range from 12 to 17 minutes.

Participation in the study will be voluntary, and participants will be allowed to withdraw from the study at any moment. The research protocol follows the CONSORT-EHEALTH V1.6 Guidelines [22]. The study will be conducted according to the principles stated in the Declaration of Helsinki (59th WMA General Assembly, Seoul, 2008).

### Measures and Design

After completing the sociodemographic form, participants will be asked to report if they suffer from a chronic disease and how much the disease impacts their perceived vulnerability to COVID-19. Participants will also be asked to report their working situation, recent changes in occupational status due to COVID-19 restrictions, and if they have prior experience with relaxation techniques. Then, participants will be asked to complete 3 self-assessment questionnaires aimed at measuring their current level of anxiety, their tendency to worry about physical signals and sensations, and the degree of attention they pay to their bodily feelings.

To assess the abovementioned aspects, the following questionnaires will be used: the State-Trait Anxiety Inventory form-trait subscale (STAI-Y) (20 items on a 4-point Likert scale from 1=not at all to 4=very much) [23,24]), which assesses trait anxiety; the subscale physical concerns of the Anxiety Sensitivity Index-3 (ASI-3) [25,26], composed of 6 items that require them to rate how much they worry about physical sensations on a 5-point Likert scale from 1=very little to 4=very much; and finally, the Body Vigilance Scale (BVS) [27], a 4-item scale in which they will describe how much they usually pay attention to body sensations on a scale from 0=”not at all like me” to 10=“completely like me”. In the fourth item, participants will be required to rate their attention to 15 body sensations that are the core physical symptoms of panic attacks [28].

After completing the questionnaires, participants will be randomly assigned to one of the three experimental groups via the randomization procedure within Qualtrics. Specifically, in each experimental condition, participants will receive a 7-minute recorded audio clip aimed to promote a state of awareness and relaxation. In the first experimental condition (ie, square breathing), participants will hear a recorded voice that guides the regulation of breathing frequencies with the aim of making every breathing act (inhalation, holding breath, exhalation, and holding breath) last the same amount of time (4 seconds). In the second experimental condition (ie, body scan meditation), an audio clip with a voice that guides the participant’s attention through every part of the body will be presented, and the listener will be invited to feel tensions and unpleasant feelings and to let them go. Both tracks were recorded by a trained mindfulness and yoga expert in collaboration with a psychotherapist and were pretested on 4 participants to assess the ease and the perceived effectiveness of the exercise. In the third experimental condition (ie, natural sounds), participants will be stimulated by a prerecorded audio clip of natural sounds. All the audio clips will be preceded by instructions on the recommended place and body position for the exercises.

As pre-post measures, before and after the audio stimuli, the participants will be asked to self-rate their perceived relaxation level, perceived stress level, or psychomotor activation degree, to rate how concerned they feel about COVID-19, and to rate 3 specific features of their emotional state. Specifically, participants will be also asked to rate on a 3-item Visual Analogue Scale (VAS) (0=not at all to 10=completely) how relaxed they feel, how stressed/activated they feel, and how much their thoughts related to COVID-19 scare them; furthermore, they will complete the Self-Assessment Manikin (SAM) [29] for emotional states, which is a 3-item visual scale (valence, intensity/arousal, and dominance) commonly used to quantify properties of a person’s overall emotional state on a scale of 1 to 5 images. Immediately after listening to the audio, participants will also be asked if they heard the entire audio track, a part of it, or no part.

Finally, all the participants will have the opportunity to describe their personal experience and to provide suggestions for future changes. Specifically, participants will be asked to write a short paragraph answering 2 open-ended questions about their personal experience with the exercise (“Did you enjoy or dislike the experience with the audio clip?”) and any changes they would appreciate (“Would you change something in the audio clip?”).

### Data Analysis

Group differences in demographic data and pretreatment measures will be analyzed with one-way analysis of variance (ANOVA) followed by *t* tests with Bonferroni corrected *P* values and chi-square tests. Differences in questionnaire scores (ie, STAI-Y, ASI-3, BVS) between groups will be examined using the same analysis. STAI scores will also be compared to clinical cutoffs. The internal consistency of the scales (Cronbach α) in our sample will also be assessed.

As the main aim of this study is to test the difference in efficacy between audio clips, our main analysis will be one-way ANOVA on gain relaxation scores [30], with 3 groups and fixed effects and with no interaction. According to our main objective, we performed a priori sample size calculation, considering a 0.25 effect size on the level of relaxation, with a high statistical power (0.95) and an alpha of .05. Considering the specified values, we will need a total sample size of 252 participants with complete surveys to reach the desired statistical power (84 per group). In view of the possibility of attrition of participants, which may occur in the present electronic health (eHealth) trial in the form of incomplete questionnaires or dropout before listening to the complete audio clips, we estimate that we will obtain incomplete data for 30% of the participants who will start the survey by clicking on the link and who will not continue with the questionnaires; thus, we should register a total of 328 participants.

Independent sample *t* tests of the relaxation level between paired groups will also be carried out on participants who will complete the entire survey (eg, without considering participants who dropped out before the randomized exposure to the audio clips).

The same analysis will be conducted for the participants’ perceived stress and fear related to COVID-19 thoughts, assessed with the VAS continuous scale, and for their emotional states, measured through the SAM. The between-group post-exercise Hedges g effect size (CI 95%) will be computed. As the randomization will be automatically performed by Qualtrics, the researchers who analyze the data will be blinded to which audio clip participants received.

Furthermore, we will perform other explorative analyses to test if and to what extent other covariates impact the efficacy of the proposed techniques. Specifically, we will test if having job issues or a chronic disease has an impact on the efficacy of the techniques.

All the aforementioned analyses will be performed in SPSS version 26.0 (SPSS, Inc., Chicago, IL).

Lastly, qualitative reports on subjective experiences and suggestions will be analyzed to understand the participants’ subjective experiences, to evaluate the perceived efficacy of the audio, and to identify possible ameliorations of and issues with the proposed stimuli. Practical advice for future studies will be given accordingly.

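### The main analysis leaves the collected pre-clip rating out as a covariate; ANCOVA on the post-clip rating would be at least as precise in large samples, at no data cost

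*Protocol article*

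**What the plan says.** Data Analysis in the protocol article sets the main test: "our main analysis will be one-way ANOVA on gain relaxation scores [30], with 3 groups and fixed effects and with no interaction". No baseline covariate is named. The same analysis is carried over to perceived stress, fear related to COVID-19 and the three SAM items, which makes six outcomes in all. The section also plans t tests of the relaxation level between pairs of groups and a between-group Hedges g on the post-exercise score, with a 95% CI.

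Measures and Design shows that the baseline value exists: "As pre-post measures, before and after the audio stimuli, the participants will be asked to self-rate their perceived relaxation level". The item is part of a "3-item Visual Analogue Scale (VAS) (0=not at all to 10=completely) how relaxed they feel". Assignment is random: "participants will be randomly assigned to one of the three experimental groups via the randomization procedure within Qualtrics".

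The sample size is derived "considering a 0.25 effect size on the level of relaxation", "with a high statistical power (0.95) and an alpha of .05", and the result is "we will need a total sample size of 252 participants with complete surveys to reach the desired statistical power (84 per group". The covariate analyses listed afterwards are exploratory. The specific ones are job issues and chronic disease; the pre-clip rating is not mentioned.

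**The concern.** Subtracting the pre-clip rating from the post-clip rating amounts to assuming that one extra point at baseline predicts exactly one extra point afterwards. On a bounded single-item rating the slope is likely to be smaller, because of rating noise and because someone near the top has little room to rise. Where the slope is not 1, the gain remains correlated with baseline. Two things follow. The residual variance is larger than it need be. And a chance difference in baseline between groups carries through into the realised gain comparison.

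ANCOVA of the post-clip rating, with the pre-clip rating as covariate, estimates the slope from the data. It needs only values that anyone with a gain score has already given. What is at stake is precision on up to six outcomes, and possibly the margin for losing completers.

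**Working it through.** **Inputs.** From Data Analysis: three groups, f = 0.25 (read as Cohen's f), alpha 0.05, power 0.95, N = 252. Assumed, because the documents give neither: the pre-post correlation rho (0.3, 0.5, 0.7) and the ratio of post to pre SD (1 in the main calculation, then 0.7 to 1.4).

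**Step 1: the plan's own figure.** For a one-way ANOVA the noncentrality is lambda = N × f², with 2 and N − 3 degrees of freedom. At N = 252, lambda = 252 × 0.0625 = 15.75 and power is 0.951. At N = 249 power is 0.949. So 252 is the smallest multiple of 3 that reaches 0.95, and the stated size is reproduced with f applied directly to the score that is tested.

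**Step 2: variances.** Let s_pre and s_post be the within-group SDs.

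- Var(gain) = s_pre² + s_post² − 2·rho·s_pre·s_post
- Var(ANCOVA residual) = s_post²·(1 − rho²)
- Difference = (s_pre − rho·s_post)², which is never negative

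The last line is the basis for saying that ANCOVA is never less precise in large samples, whatever the SDs. With equal SDs the ratio gain/ANCOVA is 2(1 − rho)/(1 − rho²) = 2/(1 + rho).

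**Step 3: equal SDs, f = 0.25 on the gain scale.** ANCOVA power uses f² × 2/(1 + rho) and N − 4 denominator degrees of freedom.

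| rho (assumed) | 2/(1 + rho) | gain-score N worth the same as 252 under ANCOVA | power at 252, gain | power at 252, ANCOVA |
|---|---|---|---|---|
| 0.3 | 1.54 | 388 | 0.951 | 0.995 |
| 0.5 | 1.33 | 336 | 0.951 | 0.988 |
| 0.7 | 1.18 | 296 | 0.951 | 0.976 |

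The benefit shrinks as rho rises: the ratio is 1.11 at rho 0.8 and 1.05 at 0.9.

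**Step 4: fewer completers.** The plan expects 30% incomplete data among 328 registered, and 328 × 0.70 = 229.6, about 230. At 230 the gain-score test has power 0.931. ANCOVA at rho = 0.5 has 0.980.

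**Step 5: unequal SDs.** With q = s_post/s_pre, the ratio is (1 + q² − 2·rho·q)/(q²(1 − rho²)).

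| q | rho 0.3 | rho 0.5 | rho 0.7 |
|---|---|---|---|
| 0.7 | 2.40 | 2.15 | 2.04 |
| 1.0 | 1.54 | 1.33 | 1.18 |
| 1.4 | 1.19 | 1.06 | 1.00 |

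So the benefit runs from about 140% (q = 0.7, rho = 0.3) to about 0% (q = 1.4, rho = 0.7, where the slope is 0.7 × 1.4 = 0.98).

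**Step 6: f = 0.25 on the raw-score SD instead.** With equal SDs, the gain-score test then works with f/√(2(1 − rho)) and ANCOVA with f/√(1 − rho²).

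| rho (assumed) | gain-score power at 252 | ANCOVA power at 252 |
|---|---|---|
| 0.3 | 0.86 | 0.97 |
| 0.5 | 0.951 | 0.988 |
| 0.7 | 0.997 | 0.999 |

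**Step 7: finite-sample check.** In a simulation with 84 per group and equal SDs, ANCOVA had the smaller standard error in every one of 4,000 runs at each of rho 0.3, 0.5 and 0.7. The degree of freedom it spends matters only when rho is about 0.98 or higher.

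**The case against.** The strongest reply is that nothing here is wrong. The groups are randomised, so the gain-score ANOVA is valid and unbiased over randomisations, and it reaches its stated power if f = 0.25 refers to the gain. That stands. A reader might infer that baseline imbalance biases the trial. It does so only conditionally on the imbalance that happens to occur, and the documents do not support more than that.

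Second, the size of the benefit is assumed. A reader might carry away 18% to 54% more participants as an established figure. It comes only from rho between 0.3 and 0.7 with equal SDs; Step 5 shows how far it moves. Nor can one say that precision is lost on every outcome, since a slope close to 1 leaves almost nothing to gain. This stands too.

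Third, a reader might infer that the study was sized on the level of relaxation and then tested on the gain. The sizing sentence follows directly on the one that names the gain-score ANOVA, and the phrase may simply name the outcome. The mismatch is one possible reading. Even on that reading the two analyses differ little at rho 0.7.

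Whether an SAP exists does not answer the core point, because the article itself fixes the analysis. The baseline significance tests and the choice of further covariates are separate matters on which this point does not depend.

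**Conclusion.** The point holds as a free improvement. The plan fixes an analysis that is valid but leaves a collected baseline unused as a covariate, and in large samples the alternative cannot be less precise. With f on the gain scale and equal SDs, the rise in power at 252 is modest, because the plan already starts from 0.951. The gain is of more use if completers fall to about 230, or if the 0.25 was meant on the raw-score SD and rho is low. No conclusion of the trial is shown to depend on the change. Every figure beyond the reproduced 252 rests on an assumed correlation and SD ratio, and should be reported as such.

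**What to change.** By a dated amendment, made before outcome data are examined:

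1. Make the main analysis a linear model of the post-clip rating on group, with the pre-clip rating of the same item as covariate. Use it for relaxation, stress, COVID-19 fear and the three SAM items.
2. Take the pairwise group contrasts and the standardised effect sizes with 95% CI from that model. Otherwise the overall test would be adjusted while the t tests on the relaxation level and the post-exercise Hedges g stayed unadjusted. The expectation that guided clips outperform natural sounds rests on those contrasts.
3. Keep the gain-score ANOVA as a sensitivity analysis.
4. State whether f = 0.25 is defined on the SD of the gain or of the raw rating.

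Further covariates are optional. The change needs no new data, participants or software, since SPSS version 26.0 fits the model. Its cost is the amendment itself: recruitment began in May 2020 according to Results, so the date of the change relative to any look at outcomes has to be on record.

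### The registration target of 328 adds 30% to 252 instead of dividing by 0.70; with the stated 30% loss it yields about 230 complete surveys and power of about 0.93, not 0.95

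*Protocol article*

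**What the plan says.** All the figures are in one paragraph of the protocol article, under Methods, Data Analysis.

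- Main analysis: "our main analysis will be one-way ANOVA on gain relaxation scores [30], with 3 groups and fixed effects and with no interaction".
- Design values: "considering a 0.25 effect size on the level of relaxation", "with a high statistical power (0.95) and an alpha of .05".
- Requirement: "we will need a total sample size of 252 participants with complete surveys to reach the desired statistical power (84 per group"). The 252 therefore counts people who finish.
- Loss: "we estimate that we will obtain incomplete data for 30% of the participants who will start the survey by clicking on the link". The 30% therefore has those who start as its denominator.
- Conclusion: "thus, we should register a total of 328 participants".

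The Results paragraph of the Abstract repeats 252 (84 per group) as the number to be analysed. No other registration target appears in the article, and no sentence says that recruitment continues until 252 complete surveys are in hand.

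**The concern.** The 328 is presented as what follows from a need for 252 completers and a 30% loss among starters. It does not follow. When the loss is a fraction of those who enter, the entry number comes from dividing by the fraction retained. Adding the same percentage to the completers gives too small a number, and the gap widens as the loss rate grows.

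At stake is whether the main ANOVA reaches the size and power the protocol sets for it. If recruitment closes at the only target given and the protocol's own loss assumption comes true, it reaches neither. The comparisons between pairs of groups are restricted to people who complete the whole survey, so they lose the same participants.

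**Working it through.** **Inputs**, all from Methods, Data Analysis: 3 groups; effect size 0.25; alpha .05; power 0.95; 252 complete surveys (84 per group); 30% loss among starters; 328 to register. The text does not name the effect-size metric. I read 0.25 as Cohen's f because that reading reproduces 252.

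**Step 1: reproduce 252.** Power of the one-way fixed-effects F test comes from the noncentral F distribution with 2 and N − 3 degrees of freedom and noncentrality λ = N × f² = N × 0.0625.

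| Complete surveys N | λ | Power |
|---|---|---|
| 249 (83 per group) | 15.56 | 0.9491 |
| 252 (84 per group) | 15.75 | 0.9515 |

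The smallest balanced total that reaches 0.95 is 252, so the protocol's figure is right. It leaves almost no margin: one participant fewer per group falls just below 0.95.

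**Step 2: reproduce 328.** 252 × (1 + 0.30) = 327.6, rounded up to 328. The 30% has been applied to completers.

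**Step 3: apply the 30% as the text defines it.** Starters needed = 252 / (1 − 0.30) = 252 / 0.70 = 360. Check: 360 × 0.70 = 252. The stated target is 360 − 328 = 32 too low, and 32/360 is about 9%.

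**Step 4: what 328 delivers.**
- Complete surveys: 328 × 0.70 = 229.6, about 230, or 229.6 / 3 = 76.5 per group instead of 84.
- Shortfall: 252 − 230 = 22, about 9% of 252.
- Loss rate at which 328 gives 252: 1 − 252/328 = 0.232, or 23.2%.

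**Step 5: effect on power**, by the same method as Step 1.

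| Complete surveys N | Power at f = 0.25 | f detectable at power 0.95 |
|---|---|---|
| 252 | 0.951 | 0.249 |
| 230 | 0.931 | 0.261 |
| 229 | 0.930 | 0.261 |

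**Step 6: could chance close the gap?** If each starter independently has a 30% chance of being lost (my assumption), the number of completers among 328 is binomial with success probability 0.70. The probability of at least 252 is about 0.4%.

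**The case against.** The best defence accepts the arithmetic and disputes its importance.

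- *The 328 is a projection, not a cap.* The article gives no rule that closes recruitment at 328, and it ties power to 252 complete surveys. This is a fair reading, and the power loss does depend on recruitment ending at 328. But 328 is the only recruitment number given, and nothing says that the link stays open until 252 surveys are complete. The figure is also wrong as a projection.
- *The loss is small.* Power of about 0.93 is still high, and the detectable effect moves only from about 0.25 to 0.26. This stands. It limits the seriousness of the error but does not make the sentence correct.
- *The 30% is only an estimate.* At 23% loss 328 would be enough, and above 30% loss even 360 would not be. This also stands, and it is a good reason to stop on complete surveys. It does not reconcile 328 with the 30% that the protocol chose.
- *Starting and registering are not clearly distinguished.* If registration meant getting past the early losses, 252 would need no inflation. If it means starting, 360 is needed. Neither reading gives 328. Taking the 30% as a share of completers would give it, but the sentence names starters as the base.

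**Conclusion.** The concern holds. The sample size of 252 is correct, but the registration target derived from it is not: 360 starters are needed and 328 are stated. With recruitment ending at 328 and the protocol's 30% loss, about 230 surveys would be complete and power would be about 0.93 instead of 0.95, a fall of about 2 percentage points.

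This rests on three things: the effect size read as Cohen's f, the loss spread evenly over the groups, and 328 treated as the point at which recruitment ends. The trial would remain well powered for f = 0.25, and the endpoint, test and allocation are unaffected. The stated figures contradict one another and need correcting, but the error does not threaten the interpretation of the main result.

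**What to change.** Correct the sentence in Data Analysis in one of two ways.

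1. **Keep the requirement.** State that 252/0.70 = 360 people must start the survey, and that recruitment closes when 252 surveys are complete and not at a count of registrations. The second part also protects power if the loss differs from 30%.
2. **Keep the 328.** State that a 30% loss then leaves about 230 complete surveys, with power of about 0.93 at f = 0.25. Alternatively, state that 328 assumes a loss of about 23%, if that rate can be supported.

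The first option costs 32 more expected starters. Recruitment is through a link shared on social media (Participants and Procedure), so in practice the link stays open somewhat longer. The second needs no further recruitment and costs only a slightly less favourable power statement or a lower loss assumption. Recruitment began in May 2020 (Results). If it has already closed, the second option applies, with the actual numbers of starters and completers reported beside the plan.

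### The stated completer set for the pairwise and secondary efficacy tests also drops people lost after randomisation, and no all-randomised analysis is given

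*Protocol article*

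**What the plan says.** All references are to the protocol article.

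- **Order of events (Participants and Procedure; Measures and Design).** Participants fill in the baseline questionnaires, are randomised within Qualtrics, hear a 7-minute clip and then give the post ratings. After the clip "participants will also be asked if they heard the entire audio track, a part of it, or no part". Two open questions follow.
- **Main analysis (Data Analysis).** The text states that "our main analysis will be one-way ANOVA on gain relaxation scores". On size it says "we will need a total sample size of 252 participants with complete surveys to reach the desired statistical power (84 per group". No analysis set is named for this ANOVA.
- **Pairwise analysis (Data Analysis).** The t "tests of the relaxation level between paired groups will also be carried out on participants who will complete the entire survey". A parenthesis introduced by eg then names one kind of person left out: those who stopped before the randomised exposure to the clip.
- **Secondary outcomes (Data Analysis).** The same analysis is to be applied to stress, COVID-19 fear and the SAM ratings.
- **Attrition (Data Analysis).** It is expected "in the form of incomplete questionnaires or dropout before listening to the complete audio clips". The 30% allowance is described as people who click the link and do not go on with the questionnaires.

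**The concern.** Leaving out people who stop before randomisation does no harm to a randomised comparison. Leaving out people who stop during the clip or before finishing the post survey is different, because the assigned clip may influence whether they stay. Finishing the survey requires both, so the rule as written conditions on behaviour after randomisation.

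The three clips ask different things of the listener: paced breathing with breath holds, guided attention to bodily tension, and listening to natural sounds. It is plausible that people who are not relaxing stop sooner, and that they do so more often with one clip than another. Relaxation gain is the main outcome. If the guided arms lost more low gainers, the completer comparison would lean towards the study's own hypothesis that guided techniques do better. If natural sounds lost more, it would lean the other way.

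**Working it through.** **1. The plan's own figure.** The inputs come from Data Analysis: three groups, "considering a 0.25 effect size on the level of relaxation", "with a high statistical power (0.95) and an alpha of .05". The effect-size metric is not named, so Cohen's f is assumed. Noncentrality is λ = N·f² = 252 × 0.0625 = 15.75, with F on 2 and 249 degrees of freedom. Power is 0.9515 at N = 252 and 0.9491 at N = 249, so 252 is the smallest multiple of 3 that reaches 0.95. The figure reproduces. Changing the analysis set does not alter this target.

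**2. The planned effect in SD units.** If the two guided arms are equal and natural sounds differs by d, the SD of the three means is d·√2/3. Setting this to 0.25 gives d = 0.25 × 3/√2 = 0.53 SD of the gain score.

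**3. A selection model.** The loss rates and correlations here are assumptions, since the document gives none. Gains are normal with SD 1 and the same mean in all arms, so there is no true difference. A latent tendency to stay has correlation ρ with gain, and the lowest fraction p on that tendency is lost. The completer mean then shifts by ρ·φ(z_p)/(1 − p), where z_p is the normal quantile at p:

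- p = 0.10: 0.1755/0.90 = 0.195, times ρ
- p = 0.20: 0.2800/0.80 = 0.350, times ρ
- p = 0.30: 0.3477/0.70 = 0.497, times ρ

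**4. Spurious difference and type I error.** There are 252 completers, split in proportion to 1 − p. With n_j and m_j the size and shifted mean of arm j, and m̄ the weighted mean, λ = Σ n_j(m_j − m̄)². Type I error is the chance that the noncentral F exceeds the 5% critical value.

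| Loss, natural sounds / each guided arm | ρ | Guided minus natural | λ | Type I error |
|---|---|---|---|---|
| 10% / 20% | 0.3 | 0.3 × (0.350 − 0.195) = 0.046 SD | 0.125 | 0.059 |
| 10% / 20% | 0.5 | 0.5 × (0.350 − 0.195) = 0.077 SD | 0.349 | 0.077 |
| 10% / 30% | 0.3 | 0.3 × (0.497 − 0.195) = 0.091 SD | 0.492 | 0.088 |
| 10% / 30% | 0.5 | 0.5 × (0.497 − 0.195) = 0.151 SD | 1.366 | 0.164 |
| 20% / 20% | 0.3 or 0.5 | 0 | 0 | 0.050 |

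Against the planned 0.53 SD, the first two rows are about 9% and 15%, and the next two about 17% and 28%. The type I errors are for the omnibus F test, so they apply to the main analysis only if it too is run on completers.

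**The case against.** The strongest reply is that the document points to loss before randomisation. Its one illustration of an exclusion is people who left before exposure, and its 30% is tied to people who do not continue with the questionnaires, which precede randomisation. On that reading the loss is common to all arms and harmless. This stands in part: the 30% cannot serve as an estimate of post-randomisation loss. But the illustration is only an example. It does not narrow a rule that requires the whole survey, and it sits poorly with an attrition description that includes leaving before the clip has been heard in full.

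Several stronger readings are tempting and are not supported:

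- **That the main ANOVA is restricted to completers.** The completer sentence governs the t tests. For the ANOVA the restriction is inferred from the sample-size wording.
- **That people who heard only part of the clip are excluded.** The attrition wording counts people who drop out before hearing all of it. It does not cover someone who heard part and then gave post ratings, and the listening question has no stated analytic use.
- **That skipping the open questions excludes a participant.** The text says only that "all the participants will have the opportunity to describe their personal experience and to provide suggestions for future changes". Exclusion would follow from the most literal reading of an entire survey, and nothing else suggests it is intended.
- **That early stopping will differ by clip.** This is a plausible risk and not a documented fact. Equal loss by the same mechanism produces no bias.

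A condensed article may also leave imputation methods to a fuller document. Their absence is not the point here. The point is the analysis set that the article does state.

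**Conclusion.** The concern holds in a limited form. The completer set is explicit for the pairwise t tests, is carried to the secondary outcomes through the same-analysis sentence, and is suggested for the main ANOVA by the sizing on complete surveys. Because it includes loss after randomisation, it leaves the comparison open to bias, and no stated analysis of all randomised participants guards against that.

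The size is unknown. Under the assumed loss rates and correlations of 0.3 to 0.5, the spurious difference runs from about 0.05 to 0.15 SD, with type I error from 0.059 to 0.164. It is zero if loss is equal and arises in the same way in every arm. A reader might infer a much larger artefact by supposing that exactly the lowest gainers leave: 0.195 SD at 10% excess loss or 0.35 SD at 20%. That is an upper bound from complete dependence of loss on gain, and nothing in the document supports it. The direction is also open, since it depends on which arm loses more people.

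**What to change.** - State that only people who left before randomisation are excluded, and reconcile the parenthetical example and the attrition wording with that rule.
- For the ANOVA, the t tests and the secondary outcomes, analyse everyone randomised in the assigned group. Use every available post rating, whatever share of the clip was heard and whether or not the open questions were answered.
- Report post-randomisation loss by arm.
- Add a sensitivity analysis for missing post ratings. One option is multiple imputation from the baseline data already collected (pre-clip VAS and SAM ratings, STAI-Y, ASI-3, BVS, prior experience of relaxation techniques) with a delta shift. The shift matters, because imputation from baseline alone does not address loss that depends on the unobserved gain.
- Present completer and full-listener results as supportive.

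The cost is revised wording and modest extra analysis. Including people who heard little or none of the clip may dilute the estimated effect slightly. The target of 252 with complete data need not change.
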